## Methods

### Study design and participants

A two group pragmatic randomized controlled trial is undertaken with adolescents with CMP, with follow-up assessment at 2, 4, 10 and 12 months after start of treatment. Adolescents will be allocated to either intervention (MRP) or control (CAU) with a ratio 1:1. Patients who receive an indication for outpatient rehabilitation treatment will be invited to participate and will be randomized to either usual care (CAU) or the intervention (MRP) after informed consent is obtained. Parents will be asked to participate as well.

Estimates for the calculation of the sample size are based on the primary outcome measure, the Functional Disability Inventory (FDI). An average FDI total score of 23 (average score obtained from adolescents that were treated at the Maastricht University Medical Centre in the year before the start of this study), a standard deviation of 9.2 and an expected mean difference between intervention and control condition of 5 points on the total FDI-score were used. A difference of 5 points equals approximately a 25 % difference in mean FDI scores between intervention and control group.

Given α = 0.05, two sided testing, a power of 80 %, and anticipating 15 % loss to follow-up, a sample size of 62 participants per trial-arm was calculated. For two trial arms, this results in a total sample size of *N* = 124.

Adolescents will be recruited from 4 centres in The Netherlands: Maastricht University Medical Centre/Adelante, Laurentius Hospital Roermond, Revant Rehabilitation centre Breda and Rijndam Rehabilitation Centre in Rotterdam. Both treatments offered are embedded in the daily care process in each treatment centre, with an inclusion period of 1.5 years. Ethical approval for this trial was granted by the Medical Ethics Committee Academic Hospital Maastricht/Maastricht University, the Netherlands, NL47323.068.13/METC13-3-062.

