### Randomization and allocation concealment

Patients will be randomized by minimization after informed consent is obtained. Minimization [41] was chosen to balance treatment centre, sex and age factors within the study. To execute the randomization procedures a validated electronic randomization system (ALEA, offered by the Clinical Trial Centre Maastricht, CTCM) will be used. Randomization and treatment allocation are completely independent of the study and blinded for participants including parents and all researchers, including raters and at that moment for caregivers and the consultant in rehabilitation medicine. After treatment allocation is revealed, blinding cannot be maintained for care givers. Adolescents and parents will be kept naïve concerning the comparison between the interventions. The research team remains blinded during the course of the study. Data collection is also blinded.

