#### Effect evaluation

Differences after 8 and 16 weeks of treatment will be calculated (short term outcomes), as well as long term outcomes at 10 and 12 months. A linear mixed models approach for calculating differences between baseline and the final follow-up at 12 months will be used. This method used both fixed and random effects in the same analysis. It handles naturally unbalanced data as e.g. uneven spacing of repeated measures and allows analysing the relationship of predictor covariates with the dependent variable (FDI-score). It also accounts successfully for the observed pattern of dependences in the measurements. Appropriate covariates (for the primary outcome potential important imbalances in baseline variables) will be identified in a univariate regression analysis. Before starting the analysis the baseline score of the dependent variable FDI-score and all identified covariates will be centred by subtracting the group mean.

In a first step a fixed effects model will be run and in a second step random effects will be added. Insignificant covariates will then be stepwise removed from the model. Model fit will be assessed with the help of the Bayesian Information Criterion (BIC) and the -2Log likelihood [62].

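### The primary FDI model picks and drops covariates on the data, so the minimisation factors (centre, sex, age) are not guaranteed a place in it

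*Protocol article*

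**What the plan says.** The section on randomization and allocation concealment states that minimisation "was chosen to balance treatment centre, sex and age factors within the study". Allocation is 1:1 across four centres.

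The Effect evaluation section specifies a linear mixed model and builds its covariate set in stages. Entry: "Appropriate covariates (for the primary outcome potential important imbalances in baseline variables) will be identified in a univariate regression analysis". Centring: "the baseline score of the dependent variable FDI-score and all identified covariates will be centred by subtracting the group mean". Fixed effects are fitted first and random effects added. Removal: "Insignificant covariates will then be stepwise removed from the model". Neither the screen nor the removal step has a stated threshold. Centre, sex and age are not mentioned in that section, whether as required terms or as exclusions.

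The sample size is a plain comparison of two means that counts on no covariate gain: "a standard deviation of 9.2 and an expected mean difference between intervention and control condition of 5 points on the total FDI-score were used", with 62 per arm after allowing for 15% loss.

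**The concern.** Minimisation forces the arms to be alike on centre, sex and age. The treatment difference then varies less from trial to trial than under simple randomisation, and a model containing those factors reflects this in its standard error. A model without them reports too large a standard error whenever they predict FDI. The test is then conservative, and precision gained by the design is not used.

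The entry rule sits awkwardly with this design. It describes candidates as "for the primary outcome potential important imbalances in baseline variables", and minimisation makes imbalance unlikely in exactly these three variables. Read literally, the rule is most likely to pass over the factors that constrained the allocation.

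In addition, the removal step uses significance in the outcome model. The covariates behind the primary estimate are therefore settled only once outcomes are in the model, and without stated thresholds more than one final model could be defended.

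**Working it through.** **The plan's own figure.** Inputs from Study design and participants: difference 5, SD 9.2, two-sided α 0.05, power 80%, loss 15%.

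n per arm = 2 × [9.2 × (1.960 + 0.842) / 5]² = 53.15, rounded up to 54. Then 54 × 1.15 = 62.1, which matches the stated 62 per arm and N = 124. (Dividing instead, 53.15 / 0.85 = 62.5, gives 63.) The figure reproduces, and it uses no covariates.

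**Reading A: entry by imbalance between arms.** Let R² be the share of FDI variance explained by centre, sex and age together. The article does not give it, so it is varied. Evaluable patients: 62 × 0.85 = 52.7 per arm, so SE = 9.2 × √(2/52.7) = 1.792. With perfect balance on the factors:

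- type I error with factors omitted = 2Φ(−1.96/√(1−R²))
- power with factors omitted = Φ((5 − 1.96 × SE)/(SE × √(1−R²)))
- power with factors kept = Φ(5/(SE × √(1−R²)) − 1.96)

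For R² = 0.10: √0.90 = 0.949 and SE × 0.949 = 1.700. Type I error is 2Φ(−2.066) = 0.039. Power is Φ(1.487/1.700) = 0.81 with the factors omitted and Φ(2.941 − 1.96) = 0.84 with them kept.

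Real minimisation does not balance perfectly, so the rule was also simulated: 106 completers, an assumed 0.8 biased coin, screening at p < 0.10, removal at p > 0.05 (all assumed), baseline FDI uninformative, ANCOVA at one time point as a stand-in for the mixed model, and 4000 runs per cell. Simulation error is √(0.05 × 0.95/4000) = 0.003 for type I error and √(0.8 × 0.2/4000) = 0.006 for power.

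| Assumed R² | Type I, formula | Type I, simulated | Power omitted / kept, formula | Power imbalance rule / kept, simulated |
|---|---|---|---|---|
| 0 | 0.050 | no miscalibration | 0.80 / 0.80 | about 0.79 / 0.77 |
| 0.05 | 0.044 | 0.047 | 0.80 / 0.82 | 0.79 / 0.80 |
| 0.10 | 0.039 | 0.037 | 0.81 / 0.84 | 0.80 / 0.82 |
| 0.20 | 0.028 | 0.030 | 0.82 / 0.88 | 0.81 / 0.88 |
| 0.30 | 0.019 | 0.022 | 0.84 / 0.92 | 0.83 / 0.91 |

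With the factors always kept, simulated type I error was 0.047–0.057 at every R², nominal apart from simulation error.

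**Reading B: entry by association with FDI, then backward removal.** Prognostic factors mostly survive. At R² = 0.20, with five factor degrees of freedom (three for centre, one each for sex and age) and 100 residual, F = (0.20/5)/(0.80/100) = 5.0, which is clearly significant. Simulated type I error is 0.044–0.054, and power is within about 1 percentage point of the fixed model (0.870 against 0.876 at R² = 0.20).

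**Selection among irrelevant candidates.** With 5, 10 and 15 pure-noise covariates, type I error is 0.053, 0.055 and 0.059 when they are selected on outcome, and 0.050, 0.053 and 0.055 when selected on imbalance (15,000 runs each).

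**The case against.** The strongest reply is that nothing in the article removes centre, sex or age. A reader might infer from the rule that the minimisation factors are left out and that the primary test is therefore miscalibrated and underpowered. The text does not support that. It leaves their inclusion open, and the univariate regression can be read just as naturally as a screen on association with FDI, since the same paragraph has just spoken of covariates in relation to the FDI score. Under that reading the effect is negligible. Nor does the removal sentence by itself cause the conservative error: strongly prognostic factors would survive it. The error arises from entry by imbalance.

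Three further points stand. The loss of power is relative to a better model, not to the plan, because even with the factors omitted power stays close to 80%. The calculation is for a single-time-point comparison, whereas the plan is a repeated-measures model; what counts there is the variance that the factors explain beyond baseline FDI, which may be smaller than the shares assumed here. And an imbalance screen uses only baseline data, so on that reading only the removal step looks at outcomes.

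It is also tempting to say that baseline FDI is at risk of removal and that forcing it in would raise power to about 90%. The centring sentence lists baseline FDI separately from the identified covariates, which suggests that it enters in its own right. A baseline with a worthwhile correlation would survive removal in any case. That gain is not credited to the fix.

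Two defences do not succeed. This is not detail left to an analysis plan: the article states a selection procedure, and a plan that fixed the model would contradict it. The research team's blinding limits the freedom to choose among models but does not expressly cover the analysis, and it does not make the covariate set prespecified.

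**Conclusion.** The point holds as one about specification. The covariate set of the primary analysis depends on the data, and the three factors used in allocation are not secured in it.

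The size is conditional. It needs both entry by imbalance and factors that predict FDI. Then type I error is about 5%, 4.4–4.7%, 3.7–3.9% and 2.8–3.0% at assumed R² of 0, 0.05, 0.10 and 0.20, and power for 5 points is about 0 to 7 percentage points below the adjusted model, though still near the planned 80%. With entry by association with FDI, or with factors that are not prognostic, the effect on error and power is close to nil. Inflation from screening many irrelevant candidates reaches about 5.9% at most.

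Confidence is high that the rule as written should be replaced. The numerical consequence can only be given as a range, because the article contains no figure for prognostic strength. The wording should be corrected; the flaw does not invalidate the trial.

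**What to change.** State the primary mixed model in advance: arm, time, arm-by-time, baseline FDI, centre, sex and age, all kept regardless of observed imbalance or significance. Delete the univariate screen and the stepwise removal from the primary analysis. Any further baseline variable that looks imbalanced goes into a sensitivity model labelled as such.

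The cost is a change of wording. All the variables are already recorded and N = 124 stands. The covariates use six degrees of freedom (three for centre, one each for sex, age and baseline FDI) out of about 105 evaluable patients (2 × 52.7). If the factors turn out not to be prognostic, the price is small: simulated power of 0.77 against about 0.79 without covariates, part of which may be simulation error.

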#### Economic evaluation

In the economic evaluation costs and effects of the intervention condition (MRP) and the control condition (CAU) will be calculated and compared, using a societal perspective. Total costs will be estimated using a bottom-up approach, where information on each element of service use is multiplied by an appropriate standardized unit cost and summed to provide and overall total cost. For the cost valuation, standardized cost prizes will be used from the Dutch manual for cost analysis in health care research [63]. Productivity losses will be calculated based on the Human Capital Approach.

At baseline resource use prior to the study will be measured, to allow this use as a covariate in the analysis, which enables correction for possible cost differences at baseline [64]. Cost per patient year (= participant year) will be calculated.

Intended, both a cost-effectiveness analysis (CEA) and a cost-utility analysis (CUA) will be performed. For the CEA the cost-effectiveness ratio will be stated in terms of cost per 5 points of improvement on the Functional Disability Inventory (FDI). For the CUA the cost-utility ratio will be stated in terms of cost per Quality Adjusted Life Year (QALY) gained, as measured by the EQ5D-Y [65]. Bootstrap re-sampling techniques will be used to test for differences and uncertainty in cost and effects between MRP and CAU.

#### Process evaluation

To evaluate treatment fidelity, audio or video recordings will be analysed of treatment sessions of both interventions conditions [42]. From these recordings, a random sample will be taken for analysis. The recordings are rated for protocol adherence, contamination, and differentiation [42]. Ratings will be performed by 2 raters, independent of this trial and blind to the study hypotheses. To enable rating, a Treatment Fidelity Checklist is developed where raters can indicate whether a treatment-element took place or not [57]. The percentage of deviation from the allowed treatment-elements is compared between the intervention and control condition by logistic regression analysis.

The data from the Credibility/expectancy questionnaire and the measures of patient/family centeredness (GYV-20 and MPOC-20) of the provided treatment will be used to evaluate differences in credibility and expectancy at the start of the treatment, and treatment satisfaction at the end of treatment.

## Discussion

Research on treatment options for adolescents with CMP is still in its infancy, but multidisciplinary treatment for this patient group seems to be a promising treatment approach. A limited number of studies have been performed to study the effectiveness of multidisciplinary treatments on improving functional ability [66–70]. Although several pre- and post-treatment comparisons have been performed, to our knowledge only few studies have compared different treatment options with each other. Another important element in adolescent treatment is the participation of parents, again, with limited evidence available on the effectiveness of parental interventions [17, 22, 38].

There is an urgent need for more research. Therefore, a pragmatic multicentre randomized controlled trial (RCT) was established to compare a new multimodal rehabilitation program with care as usual. For this study a more pragmatic approach is chosen. Schwarts and Lellouch [71] use the term ‘pragmatic’ to describe studies designed to choose between options of care, as opposed to ‘explanatory’ studies that test causal research hypotheses. Our aim is to compare the new treatment approach to existing practice to determine whether or not the new approach can be added to the treatment options existing presently. This approach led to some design choices that were made to maximize the applicability of the results to usual care settings.

To include a wide range of participants eligibility criteria are focused on the inclusion of all adolescent participants that would normally receive an indication for rehabilitation treatment. This should lead to the inclusion of a heterogeneous group of participants, very similar to the patients that are seen in current clinical practice.

Adolescents aged 12–21 years old are eligible to participate in the trial. Paediatric rehabilitation services are in principle provided up to the age of 18 years old. Most studies on treatments for adolescents include participants up to the age of 18 years old. The range of 12–21 years was chosen according to Kaplan’s [72] definition of adolescent life stage, starting with early adolescence at 12 years old, ending of late adolescence at 21 years old. Furthermore, research has shown that up to the age of 21 years, brain functions are still developing [73]. Therefore, interpretation of cognitive and behavioural processes can still be sensitive to change and can best be seen in to context of adolescence instead of adulthood. Additionally, in the Netherlands only 20 % of the 15–20 year olds are part of the working population, so for the largest part of this age group, their daily social and physical activities are more in line with the school-attending adolescents than with the working adult population.

To our knowledge, 2B Active is one of the first studies performing an economic evaluation on outpatient treatment and follow up, focussing both on the cost of the intervention itself and on patient and family costs. No measurement instrument existed that measured both adolescent and parent costs of the rehabilitation trajectory and follow-up. Therefore, a cost diary was developed to measure both medical consumption and productivity losses (work and school absenteeism) after completion of the rehabilitation program.

To summarize, several design choices that have been made may influence the balance between internal validity and external validity of the study. By studying the new intervention in a pragmatic way and in the setting in which the MRP treatment is intended to be offered, the results will be more generalizable to daily practice of rehabilitation care. Including a heterogeneous group of patients and analysis according to ITT may lead to results that are not over-estimated since real practice daily difficulties are incorporated in the trial results.

## Abbreviations

ARCS, adult responses to children’s symptoms scale; CAU, care as usual; CDI, child depression inventory; CEA, cost-effectiveness analysis; CEQ, credibility/expectancy questionnaire; CMP, chronic musculoskeletal pain; CUA, cost-utility analysis; FDI, functional disability inventory; FDI-P, functional disability inventory-parent report; FOPQ-C, fear of pain questionnaire- child version; FOPQ-P, fear of pain questionnaire-parent report; GA, graded activity; GE, graded exposure; GYV-20, giving youth a voice questionnaire; HMS, hypermobility syndrome; MATD, method of assessing treatment delivery; MPOC-P-20, measure of processes of care parent version short form; MRP, Multimodal Rehabilitation Program; PCS-C, pain catastrophizing scale – child version; PCS-P, pain catastrophizing scale-parent version; PHODA-Youth, photograph series of daily activities for youth; QALY, quality adjusted life year; QLA-CP, quality of life in adolescents with chronic pain; RCT, randomized controlled trial; VAS, visual analogue scale
